### Intervention and implementation strategies

The goal of this intervention is to support primary care practices in adoption of actionable strategies aligned with priority recommendations of evidence-based activities (Table 1) for breast cancer survivorship care. To accomplish this, multi-component implementation strategies (Table 2) will be tailored to the unique needs of each clinic; these may include practice facilitation, [60–67] expert consultation, [68, 69] collaborative learning events, [60, 70–72] audit and feedback, [73, 74] and a learning evaluation [75]. Core components of this intervention include a learning collaborative among participating sites and a participatory engaged practice model in which practices are asked to determine what elements of survivorship care are most acceptable and feasible for their local context.

**Table 1 Tab1:** ACS/ASCO Breast cancer evidence-based activities for practice customized implementation of survivorship care recommendations

Evidence-Based Symptom and Risk-Based Care Recommendations	Assess	Treat, screen or do^a^	Counsel/ provide education	Provide referral^a^
**Late and Long-term Effects**				
Fatigue	√	√		
Cognitive impairment	√	√		
Cardiotoxicity			√	
Distress/depression	√	√		
Pain and neuropathy	√	√		
Sexual health			√	√
Premature menopause	√	√		
**Lifestyle**				
Smoking cessation	√	√	√	
Obesity			√	
Physical activity			√	
Nutrition			√	
**Surveillance and Screening**				
Screening for recurrence	√	√	√	
History and physical	√	√		
De-implement MRI as low risk patients		√		
Genetic counseling for family history				√
Adjuvant endocrine therapy screening			√	
Cervical cancer screening		√		√
Colorectal cancer screening		√		

^a^Measurable in a searchable field in Electronic Health Record (EHR)

**Table 2 Tab2:** Timeline for intervention activities & implementation assessment

Initial 13 Practices Waitlist Controls – 13 Practices	Year in months											
**Intervention Activities**	**1**	**2**	**3**	**4**	**5**	**6**	**7**	**8**	**9**	**10**	**11**	**12**
Learning collaborative	√											√
Practice facilitation	√	√	√									
Academic detailing/expert consultation	√	√	√	√	√	√						
Audit and feedback	√	√	√									
**Assessments**												
RWJ Barnabus BC EHR abstraction	√					√						√
Qualitative interviews with practice members and patients	√	√	√			√						√
Practice observation	√					√						√
Practice Staff Questionnaire	√					√						√

Practices will participate in a Learning Collaborative, beginning with a Kick-Off Meeting that will include opportunities for peer and traditional learning from expert faculty. A series of informational and motivational sessions will be led by members of our steering committee and project team. At least one physician and a project quality improvement (QI) champion from each practice will be invited to attend and work with the practice facilitator to develop a practice-specific intervention plan. We have also assembled an Implementation Advisory Committee (IAC) of internationally renowned health care opinion leaders and patient advocates engaged in cancer survivorship. The IAC will be convened throughout the study to provide guidance and feedback. At the initiation meeting, practices will be oriented to the rationale for implementation of evidence-based breast cancer care delivery in primary care. Practice members will then be asked to evaluate priority recommendations for appropriateness, feasibility, and acceptability for adoption within their specific setting. The intervention team will work with the practice leadership to reach consensus on an adoption plan and assess practice operations to identify adaptations and needed supports for implementation based on the adoption choice. This multi-faceted strategy will help participating practices incorporate both clinical and organizational recommendations and allows the research team to develop supports to ease implementation. We will use data in both a kick-off learning collaborative and later in individual practice facilitation to educate clinicians and staff members about their important role in care for patients with a history of cancer. A second, final learning collaborative will serve as a post-intervention debrief.

Practice facilitation by a trained practice facilitator is a keystone of our implementation strategy (PCM outside motivators) [60–67]. The practice facilitator will be trained in symptom and risk management activities. An initial step for each practice will be to create a registry of breast cancer patients in the practice. RWJ Barnabas Health monitors administrative data centrally and can pull this data, serving as a resource for this activity. The facilitator will work with the practices to assess workflows, train clinicians in the use of audit and feedback for breast cancer care metrics to identify gaps in care, and provide symptom and risk management activities. Audit and feedback will be used to share audit reports from registries created by the practices with support from the practice facilitator [76]. EHR and registry data will be used to trouble-shoot data discrepancies, discuss and identify improvement plans, and monitor improvement over time.

### Learning evaluation and data collection

We will use a learning evaluation strategy in which ongoing data collection and analysis are used to optimize adoption of the intervention [75, 77]. Qualitative observations and interviews will be performed to understand: (1) the overall practice environment in which the intervention occurs; (2) contextual features that enhance or inhibit adoption of the intervention; (3) any adaptations to the intervention to conform to contextual needs; and (4) how the intervention was implemented. Our assessment will be guided by the following research questions:Which priority recommendations for breast cancer survivor care are most compatible for adoption in primary care practices? (Appropriateness and Adoption)What organizational and innovation adaptations are needed to support the integration of priority recommendations for breast cancer survivor care? (Feasibility and Fidelity)How do physicians and staff perceive the utility and suitability of the priority recommendations for breast cancer survivor care in day-to-day practice operations? (Acceptability)

To monitor implementation, a trained evaluation team member will conduct site visits at each intervention practice at baseline, 6 months, and 12 months. During these visits, we will observe work patterns and dynamics within each practice, how recommendations interface with daily workflows, how recommendations are introduced and explained to patients with a history of breast cancer, and how the recommendations affect coordination of cancer-related care with other chronic care needs. We will also observe how recommendations can be improved or optimized in each setting under current conditions. Fieldnotes will be prepared to record instances where contextual factors (e.g., physical space; organizational, clinician or patient features; care team workflows or processes) impact implementation efforts. Special attention will be paid to contextual features and interactions that were indicative of positive or negative alignments between intervention and local setting and instances where better alignments serve to enhance implementation progress (e.g., “implementation measures” as outlined in EPIS). Observational data will be captured in detailed fieldnotes and written up quarterly as case summaries for each practice and shared with our IAC for review and input.

During evaluation site visits, serial, open-ended key informant interviews with clinic members will be conducted. Interviewees will be purposefully selected based on observations during site visits that identify individuals who have the best insights on different aspects of the intervention. We seek to understand ongoing implementation issues and any contextual features that lead to both adoption and modifications to recommendations, and any impact of modifications on intervention effectiveness. These data are consistent with our conceptual framework (e.g., PCM “motivators/ resources for change” and EPIS “intervention characteristics”). Interview data relating to the fit of the intervention to the primary care context will then corroborated by observational fieldnotes taken during site visits. In addition, during the initial implementation and follow up assessment periods, we will conduct approximately 3–5 Zoom or telephone-based individual depth interviews per practice with patients with a history of breast cancer identified through medical records or by practice staff members [78, 79]. Interviews will focus on experiences of these patients in the practice and contextual features affecting their experience receiving cancer-related recommendations and referrals. This is consistent with EPIS “outer setting” and “intervention characteristics” and interrelationships between context and intervention as described by the PCM. Recorded interviews will use a semi-structured interview guide and be transcribed for analysis.

### Process data outcomes

During the initial meeting, we will ask practice members to assess the appropriateness, feasibility, and acceptability of the priority recommendations to inform an adoption decision. Feasibility will also be assessed based on the ability of practices to implement a functional breast cancer registry and the ability to use audit and feedback data to address patient symptom management needs. Usability will be assessed from usage tracking data collected from qualitative fieldnotes during the learning evaluation and acceptability from responses of staff to assessments (e.g., number and type of workflow changes). Adoption will be assessed through examination of practice members and organizational intervention use (e.g., number of activities implemented, number of referrals for symptom management).

### Practice level variables

Guided by EPIS, contextual factors being measured were selected based on suggestions from clinical stakeholders, community partners, and previous literature suggesting they may influence implementation success [79–81] (Table 3). Healthcare team background factors, implementation climate, and medical clinician background will be assessed using a Practice Information Form that collects demographics, management activities, and financial information for the practice and a Practice Staff Questionnaire (PSQ) [82]. The PSQ measures clinicians and office staff perceptions of key practice attributes such as “Relationship Infrastructure,” “Facilitative Leadership,” “Teamwork,” “Work Environment,” and “Culture of Learning” [83] chosen because the literature has identified them as key mechanisms for successful organizational change and patient care improvement [84, 85].

**Table 3 Tab3:** Study assessments

	**Baseline, 6 mo. & 12 mo. post implementation**
**Practice Setting and Team-Level Variables**	
Implementation Climate	QUANT
Medical Provider Background (e.g., sex, race, years in practice)	QUANT
Facility Resources	QUAL
Organizational Readiness for Change	QUAL (+ quant)
Leadership Style	QUAL (+ quant)
Healthcare Team Communication Quality	QUAL
Patient-Provider Communication Quality (provider perceived)	QUAL
Demographics	QUANT
**Patient Background Variables**^**a**^	
Depression and Anxiety	QUANT
Cognitive Function	QUANT
Fatigue	QUANT
Pain	QUANT
Menopause	QUANT
Smoking status	QUANT
Obesity status (BMI)	QUANT
**Patient Primary Outcome**^**a**^	
# of BC follow-up items implemented	QUANT

^a^These assessments will be collected from the EHR for patients in all 26 practices during the initial and waitlist interventions to assess effectiveness. They will also be monitored at 18 and 24 months for initial intervention practices to assess sustainability

Facility resources and clinic spaces will be assessed using an observational quantitative checklist of space and resources at baseline and note any changes over the course of implementation. Qualitative interviews will address perceptions of facilities such as assets and deficits, satisfaction with facilities, and impact of facility on breast cancer follow-up care implementation.

Qualitative interviews will probe stakeholder perceptions of change in their healthcare clinic settings and systems and factors that they think will impact breast cancer follow-up care implementation. Additionally, the 12-item Organizational Readiness for Implementing Change measure will be used to examine change commitment and change readiness [86]. Leadership style will be measured by qualitative interviews and the Implementation Leadership Scale (ILS), a brief psychometrically strong measure that contains 12-items with four subscales of proactive, knowledgeable, supportive, and perseverant leadership [87]. Patient-clinician and healthcare team communication quality will be assessed through qualitative interviews asking patients, clinicians, and staff to assess their interactions.

### Patient-level outcome variables

The primary outcome variable will be breast cancer comprehensive follow-up care. This will be assessed by calculating the percentage of recommendations followed out of the total recommendations a given person is eligible to receive. Lower scores will indicate less comprehensive care. The number of recommendations may vary by patient depending on personal characteristics, like weight or smoking status. Research staff will collect data from the Electronic Health Record (EHR), conducting chart abstractions on 20 randomly selected patient records per practice at each time point. Measures of care coordination/management will be assessed from chart documentation of referral and/or treatment and screening for late and long-term effects, lifestyle, surveillance, and screening activities.

### Data analysis and learning evaluation feedback

#### Qualitative analysis

Ongoing analyses of data collected by our evaluation team will be fed back to the intervention team to inform them of progress, areas in need of contextual alignment, and opportunities for further adaptation. A working summary of emergent findings will be maintained and continuously updated as incoming data are added to the project. As a validity check of qualitative results, we will check relevant data interpretations against all new data using a constant comparison approach. We will note similarities and differences between practice sites and between successive adaptations to the intervention based on adaptations from feedback cycles as conveyed by practice members and patients with a history of breast cancer.

Intervention baseline, 6 month and 12 month quantitative and qualitative results will be summarized in brief reports with recommendations to be shared with IAC members for reflections on any changes needed. These analyses represent ongoing monitoring and feedback to inform optimal adoption of cancer follow-up care recommendations with real-time results influencing efforts to adapt recommendations to better fit local needs and contexts.

#### Quantitative analysis

The primary outcome for each patient will be the percent of recommendations followed out of those for which the patient was eligible. Descriptive statistics and visualization techniques will summarize the practice averages of these percentages, overall and by treatment group and time. Additionally, we will calculate the practice rates of providing each individual service from patients for whom the service was appropriate and compare these across treatment arms and times. In formal analyses, hierarchical linear models we will study the effect of treatment on the primary outcome. Specifically, the model will include a random effect for practice to account for intra-practice correlation between patients, effects for time (baseline/follow-up) and intervention group (intervention/control), and patient characteristics such as age, race, count of co-morbidities. To test whether the intervention affects changes in the outcome over time, we will use an F-test of the interaction between treatment arm and time. In exploratory analyses, hierarchical logistic models will examine effects of the intervention on changes over time on rates of fulfillment of individual services.

Since practices in this study will be chosen for their diversity in patient population and management systems, analyses will also be conducted separately for each practice. These analyses will allow us to qualitatively examine characteristics of practices in which the intervention was effective versus those where it was not.

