## Methods

### Participants and procedures

This study will be conducted in 26 practices recruited from 79 primary care practices in the Robert Wood Johnson (RWJ) Barnabas Health system [59]. RWJ Barnabas Health includes 207 primary care clinicians serving 73,000 patients throughout New Jersey. Practices will be randomized in pairs, by approximate size and type of practice, into 13 intervention or 13 waitlist control. The impact of this implementation will be measured using mixed methods to assess EPIS Implementation and Sustainment factors related to how organizational and contextual variables affect adoption, implementation and early sustainability for provision of follow-up care, symptom, and risk management activities at 6- and 12-months post implementation. The methods of this study have been reported using the SPIRIT guidelines (Additional file 1).

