##### Power calculations

For each individual patient, the percent of applicable recommendations that were followed will be calculated. Previous studies have seen rates between approximately 30% and 70% of individual recommendations being followed (e.g., colorectal cancer screening). Hence, we assume that the range for a vast majority of possible percentages lie between 20 and 80%, giving approximately a standard deviation of 15% (based on the Empirical Rule at with 95% of all observations falling within four standard deviations). Assuming this standard deviation, an interclass correlation of 0.1 [88], a dropout rate for practices of approximately 15%, and a mean difference in percentages between control and intervention practices of 15%, we would require 26 practices to achieve 90% power when conducting the test at the 0.05 level accounting for clustering within practice. If the interclass correlation was higher, say at 0.3, we would need to see a difference of 13% to achieve the same power with 26 practices.

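### The primary model names a random effect for practice only, so the arm-by-time test leaves out practice-by-time variation and its type I error can exceed 0.05

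*Protocol article*

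**What the plan says.** All references are to the protocol article.

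- **Participants and procedures:** the practice is the unit of randomisation. "Practices will be randomized in pairs, by approximate size and type of practice, into 13 intervention or 13 waitlist control".
- **Patient-level outcome variables:** the outcome is abstracted from charts, "conducting chart abstractions on 20 randomly selected patient records per practice at each time point".
- **Quantitative analysis:** in the hierarchical linear model for the primary outcome, "the model will include a random effect for practice to account for intra-practice correlation between patients, effects for time (baseline/follow-up") and intervention group, plus patient characteristics. For the primary question, "we will use an F-test of the interaction between treatment arm and time". No practice-by-time random effect, random slope, robust variance or denominator degrees-of-freedom method is named.
- **Power calculations:** "we would require 26 practices to achieve 90% power", "when conducting the test at the 0.05 level accounting for clustering within practice". The ICC is 0.1, with 0.3 as a sensitivity value. No correlation of practice effects over time is given.

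**The concern.** A random effect for practice, as described, shifts a practice's baseline and follow-up means by the same amount. It handles the similarity of patients within a practice, but it drops out when follow-up is compared with baseline. The model then assumes that, without any intervention effect, every practice in an arm would change by the same amount apart from chart sampling error.

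If practices change by differing amounts for local reasons, that variation belongs in the error term for the intervention effect, because whole practices were allocated. With about 11 practices per arm, chance differences in drift could then be read as an intervention effect. This is the study's sole primary effectiveness test, and the Discussion says a successful result would lead to a national dissemination study.

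The article itself gives reason to expect differing change. Strategies are tailored to each clinic, practices are chosen for their diversity, and the authors plan to contrast practices where the intervention worked with those where it did not. Differing response to the intervention is not a type I error under a strict null. It is still practice-by-time variation, and leaving it out narrows the interval.

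**Working it through.** **The plan's own figure.** The 26 practices come from the Power calculations section.

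- ICC 0.1, difference 15, SD 15: 22 independent patients per arm for 90% power. The design effect is 1 + 19 × 0.1 = 2.9, and 22 × 2.9 / 20 = 3.19. That is 4 practices per arm (5 with a t reference), about 12 in total after 15% dropout. The stated 26 is not reproduced.
- ICC 0.3, difference 13: 28 per arm. The design effect is 1 + 19 × 0.3 = 6.7, and 28 × 6.7 / 20 = 9.38. That is 10 per arm (11 with a t reference), and 22 / 0.85 = 25.9, so 26. This is reproduced, as a comparison of practice means at one time point with practice-level degrees of freedom.

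So the sizing carries the between-practice variance. It does so for a follow-up-only comparison, not for the arm-by-time test. (Why the ICC 0.1 sentence does not reproduce is a separate matter.)

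**Inputs for the check.** From the article: "giving approximately a standard deviation of 15" percentage points (variance 225), and "an interclass correlation of 0.1 [88], a dropout rate for practices of approximately 15" percent. Hence 26 × 0.85 ≈ 22 practices, 11 per arm, with m = 20 charts per practice per time point. Assumed, because the article does not give it: CAC, shown from 1 to 0.5. Also assumed: two time points, different patients at each, true effect zero, two-sided 0.05.

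**Formulas.**

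- True error mean square for the interaction: E = 225(1 − ICC) + 20 × 225 × ICC × (1 − CAC).
- Within-cell degrees of freedom: 22 × 2 × 19 = 836. Practice-by-time degrees of freedom: 22 − 2 = 20.
- Residual used by the model with a practice effect only: P = [836 × 225(1 − ICC) + 20 × E] / 856.
- Type I error = 2 × [1 − Φ(1.96 × √(P/E))]. The standard error is understated by 1 − √(P/E).

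**Worked case, ICC 0.1 and CAC 0.8.** E = 202.5 + 450 × 0.2 = 292.5. P = (836 × 202.5 + 20 × 292.5) / 856 = 204.6. √(204.6/292.5) = 0.836, 1.96 × 0.836 = 1.64, and type I error = 0.101. The SE of the effect is √(4E/220) = 2.31 points, while the model would report √(4P/220) = 1.93.

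| ICC | CAC | E | P | SE understated | Type I error |
|---|---|---|---|---|---|
| 0.1 | 1 | 202.5 | 202.5 | 0% | 0.050 |
| 0.1 | 0.9 | 247.5 | 203.6 | 9% | 0.075 |
| 0.1 | 0.8 | 292.5 | 204.6 | 16% | 0.101 |
| 0.1 | 0.5 | 427.5 | 207.8 | 30% | 0.172 |
| 0.3 | 1 | 157.5 | 157.5 | 0% | 0.050 |
| 0.3 | 0.9 | 292.5 | 160.7 | 26% | 0.146 |
| 0.3 | 0.8 | 427.5 | 163.8 | 38% | 0.225 |
| 0.3 | 0.5 | 832.5 | 173.3 | 54% | 0.371 |

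Type I error reaches 0.10 at CAC of about 0.80 for ICC 0.1 and about 0.95 for ICC 0.3.

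**Simulation (13 practices per arm, 40,000 replicates).** With the practice effect only, type I error was 0.076, 0.103 and 0.171 at ICC 0.1, and 0.145, 0.226 and 0.375 at ICC 0.3 (CAC 0.9, 0.8, 0.5). Fitted mixed models at ICC 0.1 gave 0.119 at CAC 0.8 (295 fits) and 0.170 at CAC 0.5 (347 fits). With practice-by-time variation as the error term it was 0.047 to 0.052. Changing only the degrees of freedom to the practice level, without the missing variance component, left 0.086 (ICC 0.1) and 0.204 (ICC 0.3) at CAC 0.8.

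**If patients recur.** Let q be the overlap fraction times the within-patient correlation. The first term of E becomes 225(1 − ICC)(1 − q), and the within-cell part of P is unchanged.

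| ICC | CAC | q = 0 | q = 0.25 | q = 0.5 |
|---|---|---|---|---|
| 0.1 | 0.9 | 0.075 | 0.047 | 0.022 |
| 0.1 | 0.8 | 0.101 | 0.072 | 0.044 |
| 0.1 | 0.5 | 0.172 | 0.147 | 0.120 |
| 0.3 | 0.9 | 0.146 | 0.119 | 0.091 |
| 0.3 | 0.8 | 0.225 | 0.204 | 0.182 |

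**The case against.** - **The text does not say that practice is the only random effect.** It says that the model will include one, and an article may leave covariance detail and degrees of freedom to an analysis plan. The degrees-of-freedom method is indeed open. But the article chooses to spell out the model for this test, and the structure it names does not suit the test.
- **The inflation rests on a CAC that the article does not give.** This stands. At CAC 1 the test holds 0.05. At the planning ICC of 0.1, CAC 0.9 gives only about 7.5%. The largest figures use the sensitivity ICC. All practices belong to one health system, so system-wide changes would fall into the fixed time effect. A reader might infer that the level certainly fails, and the documents do not support that.
- **The same patients may be drawn twice.** This also stands in part. The article gives 73,000 patients and 79 practices, about 924 per practice. If 2% to 4% had a history of breast cancer (an assumption), the pool would be about 18 to 37, and two draws of 20 would share roughly 54% to 100% of patients. Larger recruited practices would share fewer. The second table shows that this can remove the inflation at ICC 0.1. It does not at ICC 0.3 with CAC 0.9 or 0.8. The article plans no linkage of patients, so the offset cannot be relied on.
- **The power section says clustering is accounted for.** A reader might infer that this statement is false. It describes the sample-size calculation, and the ICC 0.3 figure does carry the between-practice variance. What is not shown is that the named analysis model does the same for the arm-by-time contrast.

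**Conclusion.** The point holds in conditional form. The named model omits the practice-by-time variance, which is the right error term when practices are randomised. Unless practices drift in parallel, the primary interval can be too narrow and the type I error above 0.05.

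With 22 practices, 20 independent charts per practice per time point and SD 15, type I error over CAC 1 to 0.5 runs from about 5% to 17% at ICC 0.1, and from about 5% to 37% at ICC 0.3. A doubling to 10% needs CAC of about 0.80 or lower at ICC 0.1, or about 0.95 or lower at ICC 0.3. Recurring patients would shrink these figures, at ICC 0.1 possibly to nothing. The structural gap follows from the text, while its size in this trial is not known.

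**What to change.** Add one sentence to the analysis section: the model has random effects for practice and for practice-by-time (or the analysis compares practice-level changes between arms), and the intervention contrast is tested with practice-level denominator degrees of freedom, by Kenward-Roger or Satterthwaite, about 20 to 24. If charts can recur across time points, link them and add a patient random effect. State the CAC assumed in the power calculation.

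The cost is a somewhat wider interval and no new data. With 11 practices per arm and 20 degrees of freedom, at ICC 0.1 and CAC 0.5 the correct SE is √(4 × 427.5 / 220) = 2.79 points, so power for the planned 15-point difference stays above 99%. At ICC 0.3 and 13 points, power is about 99% at CAC 0.8 and 89% at CAC 0.5.

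Setting a common baseline mean for the two randomised arms is an optional gain in precision and not part of the error. It multiplies the change-score variance by (1 + r)/2, where r is the correlation between a practice's baseline and follow-up means. For example, r = 20 × 0.1 × 0.8 / 2.9 = 0.55 at ICC 0.1 and CAC 0.8, a reduction of about 22%.

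### Analysing each practice separately gives uncontrolled and imprecise before/after changes, a weak basis for sorting practices into those where the intervention worked and those where it did not

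*Protocol article*

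**What the plan says.** After describing the primary hierarchical model, the Quantitative analysis section of the protocol article adds that, because practices are chosen for diversity, "analyses will also be conducted separately for each practice". It gives the purpose as being to "qualitatively examine characteristics of practices in which the intervention was effective versus those where it was not".

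Three other statements determine what such an analysis can show:

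- Participants and procedures: "Practices will be randomized in pairs, by approximate size and type of practice, into 13 intervention or 13 waitlist control". The practice is the randomised unit.
- Patient-level outcome variables: the outcome comes from "conducting chart abstractions on 20 randomly selected patient records per practice at each time point".
- Power calculations: the planning values include "giving approximately a standard deviation of 15" (in percentage points) and "an interclass correlation of 0.1".

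The article gives no rule for calling a practice effective. It does not mention the control arm, shrinkage or multiplicity for this step.

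**The concern.** There are two separate difficulties.

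**No control.** The primary test is the arm-by-time interaction, which removes change common to both arms. A practice analysed alone contains one arm only, so its result is a before/after change. All practices belong to one health system, so a shared shift over the year (in documentation, screening campaigns or referral routes) is plausible and would count as intervention effect. This holds whatever the effect size and whatever labelling rule is used.

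**Imprecision.** Each practice's change rests on 20 charts against 20. If estimates that noisy are cut into two groups, some practices change group through sampling error alone. A comparison of practice characteristics across the groups may then find contextual explanations for differences that are not real. The Discussion hopes the findings will inform scalable interventions and a national dissemination study, so a spurious driver of success could be carried forward.

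**Working it through.** **Inputs.** 20 charts per practice per time point, treated as independent samples because records are drawn at random each time (Patient-level outcome variables). SD 15 points, ICC 0.1 with 0.3 as the alternative, planned difference 15 points, level 0.05 (Power calculations). 13 intervention practices (Participants and procedures). Assumed here: a two-sided test, and a practice labelled effective when its own rise has p<0.05.

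**The plan's own figure.** The article gives no precision for a single practice; its only figure is 90% power with 26 practices. With "a dropout rate for practices of approximately 15" (per cent), 26 × 0.85 ≈ 22 practices remain, or 11 per arm. At ICC 0.1 the design effect is 1 + 19 × 0.1 = 2.9 and the SE of the arm difference at follow-up is 15 × √(2 × 2.9/220) = 2.44. Power at 15 points is then above 99.9%, and 90% power is reached at about 8 points (7.9 by z, 8.3 by t). The stated 90% at 15 points is therefore not reproduced at ICC 0.1. The ICC 0.3 scenario is: 91.6% power at 13 points. That mismatch is a separate matter. It is relevant here only because it makes about 8 points a difference the trial could detect.

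**One practice's change.**

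- Within-practice SD = 15 × √(1 − 0.1) = 14.2.
- SE(change) = 14.2 × √(2/20) = 4.5 points. At ICC 0.3 it is 15 × √0.7 × √0.1 = 4.0.
- 95% half-width (t, 38 df) = 9.1 at ICC 0.1 and 8.0 at ICC 0.3.
- If 13 practices share one true change, the expected extremes of their observed changes lie about 1.668 × 4.5 = 7.5 points either side of it.

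**Labels when every practice truly gains the same amount** (noncentral t, 38 df):

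| True gain | ICC 0.1: P(labelled effective) | Not effective, of 13 | ICC 0.3: P(labelled effective) | Not effective, of 13 |
|---|---|---|---|---|
| 15 | 0.90 | 1.3 | 0.96 | 0.6 |
| 13 | 0.80 | 2.6 | 0.89 | 1.4 |
| 10 | 0.58 | 5.4 | 0.69 | 4.0 |
| 8 | 0.41 | 7.7 | 0.50 | 6.5 |

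Even at 15 points and ICC 0.1, all 13 practices receive the same correct label only 0.901^13 = 26% of the time.

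**Shared trend with no intervention effect.** The documents give no trend, so this is an assumed range. At ICC 0.1, a system-wide rise of 3, 5 or 8 points would produce a significant rise in 10%, 19% or 41% of practices.

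**How much of the sorting is real.** Reliability of a practice's estimate = τ²/(τ² + 4.5²), where τ is the between-practice SD of true effects. The documents do not give τ. For assumed values of 3, 5, 7.5 and 10 points, reliability is 0.31, 0.55, 0.74 and 0.83.

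**The case against.** A reader might infer that the classification will be largely chance. The documents do not support that as a general statement. At the planned 15 points about 90% of practices would be labelled effective, and most labels would be right. Strategies are tailored to each practice and practices are chosen for diversity, so real differences in effect are to be expected. With τ of 5 points or more, over half the variance in the estimates is real.

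A reader might also infer that the study's account of what drives success rests on these labels. It does not. Site visits, fieldnotes, staff and patient interviews, questionnaires and adoption tracking all feed that account, and the step is described as qualitative.

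The p<0.05 rule is not the protocol's, and a condensed article may leave the rule to a fuller document. Every count in the table depends on it. The article does not rule out reading a practice's change against its matched pair or the control arm. Waitlist practices have a pre-intervention period of their own, and pooling 6- and 12-month charts lowers the SE to 14.2 × √(1/20 + 1/40) = 3.9.

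These points limit the size of the problem without removing it. The stated method is separate analysis, and within one practice there is no concurrent control. A waitlist practice's earlier period is a historical comparison, and a single matched practice adds its own sampling error. The SE and the interval width do not depend on any labelling rule.

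**Conclusion.** The point holds in a limited form. The separate analyses are uncontrolled because the practice is the randomised unit, and each estimate carries an SE of about 4.5 points at ICC 0.1 (4.0 at ICC 0.3). A two-way split on such estimates is fairly dependable if the true gain is near 15 points. It becomes unreliable at 8 to 10 points, where 5 to 8 of 13 equally successful practices would be put in the wrong group at ICC 0.1. Those counts assume equal true gains and a p<0.05 label. With unequal gains the answer depends on τ, which is not given.

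The primary arm-by-time test is not touched, and the labels are one input among several to the explanatory work. The change is worth making because a better-controlled estimate can be had from a model already planned.

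**What to change.** Replace the separate analyses with practice-specific effects from the planned hierarchical model:

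1. Add a random practice-by-time effect.
2. Report each intervention practice's shrunken estimate net of the mean control-arm change, with an interval.
3. Report the estimated between-practice variance with its interval. Do not make a significance test of that variance a condition for going on. With 13 practices and an SE of 4.5, a chi-square test on 12 df has only about 27% power at τ = 3 and 67% at τ = 5.
4. Use the continuous estimates, not an effective/not-effective split, in the qualitative comparison, and label that comparison exploratory.

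Subtracting the mean control-arm change removes shared trend but not a practice's own drift. The spread of changes among control practices shows how large that drift is and should be reported alongside.

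The cost is a few lines of analysis text and no new data. The real downside is that fewer practices will stand out as clear successes or failures, so the contrasts available for the qualitative work will be less sharp.
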